### 11.2 If this is a clinical trial, check the applicable phase(s) (Help Text updated 9/13):

- ☒ Phase I
- ☐ Phase II
- ☐ Phase III
- ☐ Phase IV

## 12.0 Scientific Considerations

### 12.1 Hypothesis (Help Text updated 9/13):

This study has a hypothesis:

☒ Yes ☐ No

If yes, state the hypothesis or hypotheses:

We hypothesize that participants in the SFGH Health Advocacy program will experience improved physical and emotional health (child); improved caregiver mental health; decreases in hair cortisol (child and caregiver); fewer missed school (child) or work days (caregiver); and decreases in acute care utilization (child). Additional outcomes of interest include other stress biomarkers, like salivary inflammatory cytokines and DNA genotyping and methylation.

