### 12.3 Statistical analysis:

**Descriptive Analyses & Missing Data.** Descriptive analyses will include family demographics, biomarker, child and caregiver health, and family social needs. Data will be inspected for outliers and out-of-range values. Examination of distributions may prompt transformations, where they are defensible and are a component of the best available analysis strategy. Although protocols have been designed to promote retention, some attrition is inevitable. We will perform analyses to determine whether differential attrition occurred by patient characteristics. Likelihood based approaches (e.g. GLMMs) will be used to handle missing data. This approach fits models to all available data and invoke the relative assumption that the data are missing at random.

Background demographics will be examined to describe the sample and will be included in multivariate analysis if they are related to the outcome at  $p < .2$  or associated with dropout. Correlations among variables will be examined and redundant measures will be combined or eliminated to avoid multicollinearity. We will compare participants randomized to the two groups on caregiver and child characteristics using t-tests and chi-square tests.

**Assessment of Outcomes:** We will fit regression models for cross-sectional and longitudinal outcomes. Changes from baseline to follow-up on the primary outcomes will be estimated with linear mixed models and generalized linear models with generalized estimating equations (e.g., SAS PROC MIXED, GENMOD, SAS Institute Inc., 1999). Generally, we seek to model longitudinally the trajectory of the primary outcomes as a function of time. We begin by fitting *base* models, those with intervention group and minimum covariates and, for longitudinal models, the most restricted residual covariance structures. We will then consider additional baseline demographic or family predictors, and baseline family predictors-by-time interaction in subsequent models to examine moderators of change. Similar models will be used to examine each of the primary outcomes outlined. Empirical contributions to model selection decisions will include reference to information criteria (e.g., Akaike's). We will examine change from baseline for each outcome as the dependent variable.

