The San Francisco General Hospital (SFGH) Health Advocacy (HA) intervention specifically includes implementing a navigation desk at the SFGH pediatric urgent care center. The program is available to all families presenting for care to the SFGH Primary Care Clinic. All families entering the site are offered screening for social issues affecting their health, including nutrition, housing and financial insecurity. Families with a positive screen are referred to the HA program, where navigators assist them to address each family's specific needs. Using a client management database, HA navigators follow the family over time to ensure that identified needs have been successfully addressed. The initial RCT data collection effort of the HA intervention was very successful. Results showed that participants in the intervention arm decreased needs and improved child health significantly more than the control group arm (publication pending). In this new study phase, we plan to examine the effects of the HA program on a more robust set of survey data including detailed measures of caregiver and child health and non-invasive biological data. We will collect survey responses to a broader range of health outcomes for children and their caregivers, including intermediate health outcomes like caregiver depression, work and school attendance, and biomarkers of stress IL-6/ inflammatory cytokines (oral swab collection) and hair cortisol. This work is based on existing studies showing that hair cortisol and inflammatory cytokines are important markers of socioeconomic status and social stressors.(20-23)

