### 14.6 Inclusion criteria:

- English or Spanish speaking parent or legeal gaurdian

- Parent or legal guardian accompanying an SFGH Primary Care or Urgent Care
- Clinic patient 0-17 years old
- Parent or legal guardian over or equal to 18 years old
- Parent or legal guardian resides with child in SF County
- Are not currently receiving services from the Health Advocate program or have not received Health Advocate services in the six months prior to enrollment

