If a family is randomized into the intervention group, the HARA will have access to the social needs screening results obtained through the health survey. The HARA will proceed with the health advocacy intervention following the procedures of the SFGH Health Advocacy program and attempt to address unmet needs identified by the caregiver in the survey. This involves working directly with these participants to identify and address any social needs the family may have such as access to food, living conditions and financial security. This may also include providing referrals to outside agencies, referral to legal aid within the clinic, help with applications for social benefits, or other services (See attached HARA Initial Action Plan and FollowUp Survey). Participants in the intervention group who are also ZSFG Pediatric Primary Care patients will have receipt of any direct assistance provided by the HARA documented in their child's medical record indicating services provided. All members of the intervention group will receive a written handout containing information about community resources related to the social needs we ask about in the survey.

The HARA will follow-up with members of the intervention group for a maximum of 3 months by telephone to continue to assess progress towards addressing social needs and to provide further help as needed. When relevant, HARA will send blank program forms to families or other publicly available program information via email or U.S. post to members of the intervention group. If a patient does not respond to telephone follow-ups for over 1 month, HARA may also send secure email to initiate follow-up contact.

If participant dyads are randomized into the control group, the HARA will provide the family with a written handout containing information about community resources related to the social needs we ask about in the survey.

Complete scripts for the biomarker specimen collections are found in Appendices A and B. Following surveys, hair, saliva and buccal mucosal cells will be collected non-invasively. These measures will be obtained immediately after enrollment and at the six month follow up timepoint.

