## Appendix B

### **Saliva and Buccal Mucosal Cell Sample Collection Procedure:**

As with the hair sample collection, the research assistant will collect the mother's saliva and buccal cell sample while the child is with his/her caregiver. Then the research assistant will collect the child's sample. The steps involved in collected samples of saliva and buccal cells are as follows:

1. Make sure the child or adult has no food or gum in his/her mouth.
2. Put on non-latex gloves
3. Pull open the package from one end
4. Remove one of the swabs from the tube
5. Ask child or mother to open his/her mouth; use a tongue depressor if necessary.
6. Insert the swab into the mouth and rub firmly against the inside of the cheek and/or underneath lower and upper lips.
7. Continue rubbing in broad strokes for approximately 30 seconds to 1 minute. For maximum DNA collection, expand the sampling area to both sides of the mouth and use both sides of swab.
8. Remove the swab from the mouth, slide the plastic cap over the swab handle, with the flat side of the cap facing upwards and the swab facing downwards.
9. Insert the swab into the clear plastic tube and push the cap in place.
10. Hold the cap firmly on the tube while pulling the swab handle outwards to release the swab material into the tube.
11. Close the cap; the tube is now completely sealed.
12. Insert saliva swab into mouth until saturated.
13. Remove swab and insert into plastic tube; close cap; the tube is now completely sealed.

After collection of biomarker hair and saliva/buccal mucosal cell samples, family will receive the first \$50 gift card for participation. At five months post-enrollment, research assistant will contact family by phone or email to arrange 6 month follow up visit (may occur no earlier than 5 months and no later than 9 months post enrollment). Participants will be contacted up to 5 times by phone and/or email to arrange in-person follow-up for repeat survey and biomarker collection activities.

At the six month visit, child and caregivers will meet with the Research Assistant in the same private room on 6A, an interview room located in the Clinical Research Services (CRS) facilitates located at SFGH hospital one floor below pediatric urgent care in unit 5B, or in another community location that ensures participants' confidentiality where surveys will be conducted and non-invasive biomarker specimens collected from caregiver and child (repeat of collection procedures as above.)

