**19.4 Benefits to society:**

If our hypotheses are correct, then connecting patients with health advocate navigators will decrease social needs, decrease caregivers' missed work days, and improve child school attendance, decrease hair cortisol and salivary/buccal mucosal cell inflammatory markers, and decrease avoidable health care utilization.

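### Missed school and work days are set up as change from baseline with no denominator or at-risk group; for school days this is inefficient, though not biased on average

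*Protocol*

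**What the plan says.** Protocol 12.1 words the outcome as a number of days: "fewer missed school (child) or work days (caregiver". Two other sections word it partly as attendance. Section 13.1 describes a broader set of outcomes, "including intermediate health outcomes like caregiver depression, work and school attendance", and 19.4 expects the programme to reduce caregivers' "missed work days, and improve child school attendance".

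Section 12.3 describes "linear mixed models and generalized linear models with generalized estimating equations", mainly with the primary outcomes in view, and closes with a rule of wider reach: "We will examine change from baseline for each outcome as the dependent variable". It fits models to all available data, assumes data are missing at random, and allows transformations.

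Section 14.6 admits a "Clinic patient 0-17 years old" and any parent or guardian aged 18 or over. It has no school-enrolment or employment criterion. Under 16.1, Appendix B, the follow-up visit "may occur no earlier than 5 months and no later than 9 months post enrollment".

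No section gives a look-back period, a denominator, or a rule for no school, school holidays, no job, or a job gained or lost. The surveys that hold the items are attachments and are not shown. Section 14.4 gives effect sizes only for number of social needs and for cortisol.

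**The concern.** A day can be missed only if it was scheduled. Change in missed days therefore reflects attendance only if the number of scheduled days is similar at both visits. An age range starting at birth, a visit window of 5-9 months that moves follow-up to another part of the school year, and unrestricted caregiver employment all work against that.

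For school days, differences in scheduled days fall on both arms alike. They add variance unrelated to attendance. Subtracting the baseline count also carries its noise in full into the outcome, where adjustment would use only its predictive part. At stake is power for a stated hypothesis.

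For work days the question is interpretation. Among its targets the intervention lists "social needs the family may have such as access to food, living conditions and financial security". If employment also moved by arm, a count over all caregivers would mix attendance with having a job at all.

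**Working it through.** **1. The plan's own figure.** Section 14.4 gives 362 dyads per arm, 30% attrition, 253 per arm, and at least 80% power for d = 0.25 at two-sided 0.05.
- Attrition: 362 × 0.70 = 253.4.
- Power = Φ(d√(n/2) − 1.96) = Φ(0.25 × √126.5 − 1.96) = Φ(0.852) = 0.803 (0.801 with the t distribution).

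The figure reproduces. It was not derived for missed days.

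**2. Does restricting to those at risk help by itself?** Let f be the share at risk, which the documents do not give. Suppose the others have zero change. The mean difference becomes f·d and the SD √f, so the standardised effect is d√f. With all n per arm the test statistic is centred on d√f·√(n/2) = d√(fn/2), the same as restricting to f·n per arm. At d = 0.25:
- f = 0.8: 0.71 restricted (202 per arm), 0.71 with everyone kept.
- f = 0.6: 0.58 restricted (151 per arm), 0.59 with everyone kept.

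Restriction alone gains almost nothing in power. It does change the estimate: with everyone kept, the mean difference is only f times the effect among those at risk.

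**3. How much do scheduled school days vary?** Assumed, since the protocol gives none of these: ages uniform over 0-17, no school under 5, a 74-day summer break, enrolment spread over the year, follow-up uniform over 150-274 days. Under-5s are 5/18 = 28% of the eligible age range. Child pairs with no scheduled school day at one or both visits are 45.5%, 27.7% and 27.7% for look-backs of 1, 3 and 6 months. The excess at 1 month is summer break in school-age children.

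**4. Power for school days.** As in step 3, plus a miss probability of 0.06 per school day, gamma(1) frailty between children, 506 dyads and a true 25% reduction:

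| Analysis | 1 month | 3 months | 6 months |
|---|---|---|---|
| Change from baseline | 0.27 | 0.54 | 0.86 |
| Baseline adjustment alone | 0.39 | 0.68 | 0.94 |
| Offset and baseline rate | 0.50 | 0.87 | 1.00 |

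Type I error is about 5%. The share of the gain due to baseline adjustment is 0.12/0.23 = 52%, 0.14/0.33 = 42% and 0.08/0.14 = 57%. A separate simulation that also removes weekends (400 runs) gives 0.30, 0.53 and 0.85 for the change score and 0.49, 0.82 and 0.96 for the full model. In that simulation:
- limiting the change score to children with school days at both visits gives 0.36, 0.53 and 0.86;
- an offset without the baseline covariate gives 0.43, 0.57 and 0.71, which is below the change score at 6 months.

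The offset and the covariate are needed together.

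**5. Work days, conditional only.** Suppose caregivers without a job score 0, a share e is employed, navigation adds x to employment, and missed days per worker truly fall by 20%. The all-caregiver ratio is 0.8(e + x)/e.
- e = 0.40: x = 0.05 gives 0.8 × 0.45/0.40 = 0.90; x = 0.10 gives 1.00.
- e = 0.60: x = 0.05 gives 0.87; x = 0.10 gives 0.93.

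With no effect on attendance, the spurious difference is x times mean missed days per worker: from 0.05 × 2 = 0.1 to 0.10 × 6 = 0.6 days. The documents give none of e, x or the days per worker.

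**The case against.** A reader might infer that the plan counts children without school and caregivers without work as perfect attenders, and job loss as improvement. The documents do not support that. No section says that raw counts are analysed or that a non-applicable answer is scored zero. Transformations are open, generalized linear models are already named, and an ordinary skip pattern in the unseen surveys would make these values missing. This part of the objection stands.

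It does not remove the point. If such answers are missing, the change score is undefined for anyone without school or work at either visit, and the missing-at-random assumption of 12.3 is applied to days that never existed. Neither coding corrects for summer break in enrolled children, and a transformation supplies no denominator.

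A reader might also infer that the school absence rate would be understated by about 42%. That figure needs a rate per calendar day, which the protocol never computes.

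Three further objections stand. The outcome is peripheral: it is not named in the four aims in 12.2 or in the power section, and 13.1 calls attendance intermediate. An employment effect is assumed: 16.1 mentions referrals, legal aid and benefit applications but not job placement. And a rate among those employed at follow-up conditions on something that happens after randomisation, so it cannot replace the randomised comparison.

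**Conclusion.** The point holds for school days as a matter of efficiency and definition. The protocol fixes a change score on a day count whose scheduled days differ between visits, in a sample that includes children too young for school, and names no at-risk group. The arm comparison is not biased on average. Under the stated assumptions, power would rise by about 0.14 to 0.33 depending on the look-back, about half of it from baseline adjustment and the rest mainly from the offset. These figures are illustrative: age mix, look-back and absence rate are all assumed.

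For work days, a difference in bias between arms is possible but not shown. It needs both zero-scoring and an employment effect, and the protocol states neither. What holds is that the protocol should say how caregivers without a job enter the analysis.

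This is worth correcting for a stated hypothesis, but it does not touch the outcomes on which the study is powered.

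**What to change.** In 12.3, with matching words in 12.1:

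- **School days.** Restrict to school-enrolled children. Model the follow-up count with a log-link model (GENMOD, already named) and robust standard errors. Use log(scheduled school days in the look-back, from the school calendar) as offset and the baseline rate as covariate. Add an indicator for children with no scheduled days at baseline, about 9% of all dyads at a 1-month look-back under the assumptions above. Visits with no scheduled days contribute no exposure.
- **Work days.** Keep the comparison of all randomised caregivers, adjusted for baseline, and state how a caregiver without a job is scored. Report employment at follow-up by arm beside it. Show the rate per scheduled work day among workers only as a supportive analysis, because it conditions on employment after randomisation.
- State the look-back period for both outcomes.

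The cost is a few sentences and perhaps one or two survey items (enrolled or employed; usual days per week) if they are not already asked. The downside is that children not in school leave this one outcome.

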### 12.2 \* List the specific aims:

This research phase evaluates the health impacts of the SFGH Health Advocates program. In addition to the aims of the first RCT we conducted from 2013-2015, we will measure the effects of the program on:

1. Child health measures
2. Child and caregiver stress and immunologic biomarkers, including hair cortisol levels.
3. Caregiver stress, depression and social support.
4. Caregiver health status.

### 12.3 Statistical analysis:

**Descriptive Analyses & Missing Data.** Descriptive analyses will include family demographics, biomarker, child and caregiver health, and family social needs. Data will be inspected for outliers and out-of-range values. Examination of distributions may prompt transformations, where they are defensible and are a component of the best available analysis strategy. Although protocols have been designed to promote retention, some attrition is inevitable. We will perform analyses to determine whether differential attrition occurred by patient characteristics. Likelihood based approaches (e.g. GLMMs) will be used to handle missing data. This approach fits models to all available data and invoke the relative assumption that the data are missing at random.

Background demographics will be examined to describe the sample and will be included in multivariate analysis if they are related to the outcome at  $p < .2$  or associated with dropout. Correlations among variables will be examined and redundant measures will be combined or eliminated to avoid multicollinearity. We will compare participants randomized to the two groups on caregiver and child characteristics using t-tests and chi-square tests.

**Assessment of Outcomes:** We will fit regression models for cross-sectional and longitudinal outcomes. Changes from baseline to follow-up on the primary outcomes will be estimated with linear mixed models and generalized linear models with generalized estimating equations (e.g., SAS PROC MIXED, GENMOD, SAS Institute Inc., 1999). Generally, we seek to model longitudinally the trajectory of the primary outcomes as a function of time. We begin by fitting *base* models, those with intervention group and minimum covariates and, for longitudinal models, the most restricted residual covariance structures. We will then consider additional baseline demographic or family predictors, and baseline family predictors-by-time interaction in subsequent models to examine moderators of change. Similar models will be used to examine each of the primary outcomes outlined. Empirical contributions to model selection decisions will include reference to information criteria (e.g., Akaike's). We will examine change from baseline for each outcome as the dependent variable.

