### 19.2 Steps taken to minimize risks to subjects:

All participants are advised that they have the right to decline to answer any questions that may make them feel uncomfortable.

Participation in the study is optional. There are no repercussions for non-participation. Children and caregivers consenting for the study and those who do not will receive the same clinical treatment. Participants in the study can refuse future participation at any time during the course of treatment; their samples will be removed from analyses.

Both mother and child will give their hair, saliva and buccal cell samples together in the private office with the research assistant present. The child will give his/her samples while sitting in mother's lap or in his/her own chair. At no time will the child or mother be left alone.

As it is explained to participants, collection of biological samples will help us understand how the Health Advocates program may impact physical health.

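### Section 12.3 promises likelihood-based, missing-at-random handling of all available data, but its change-score outcome and its unweighted GEE do not deliver it

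*Protocol*

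**What the plan says.** Section 12.3 sets the missing-data approach: "Likelihood based approaches (e.g. GLMMs) will be used to handle missing data". It adds: "This approach fits models to all available data and invoke the relative assumption that the data are missing at random".

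The same section then fixes the estimators. Changes in the primary outcomes "will be estimated with linear mixed models and generalized linear models with generalized estimating equations". It does not say which outcome goes to which model, and it gives no weighting or imputation for GEE. Base models start from "for longitudinal models, the most restricted residual covariance structures", and later selection refers to Akaike's criterion. The section closes by making each outcome's change from baseline the dependent variable.

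Elsewhere in the protocol:
- Section 11.1 has two measurement occasions, baseline and 6 months.
- Section 14.4 expects 30% attrition, leaving 506 of 724 dyads. It bases power on a two-sided t-test of change, with d = 0.25. It treats number of social needs and cortisol as primary outcomes.
- Section 19.2 says of participants who refuse further participation that "their samples will be removed from analyses".

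**The concern.** A likelihood analysis is protected under MAR because a dropout's baseline value stays in the model and, through its correlation with follow-up, informs the missing value. A change score built from two visits discards that baseline value: no follow-up means no record. Fitting a mixed model to change scores does not bring it back.

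GEE is a different case. It keeps the baseline record, but how far that record corrects the follow-up mean depends on the working correlation. With independence there is no correction at all.

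The plan therefore offers routes that can give different answers from the same data. Dropout that differs by arm is plausible in this design. Section 16.1 gives intervention families up to 3 months of navigator telephone contact, while control families are offered advocacy only after the 6-month visit. At stake is the between-arm comparison on the primary outcomes, with a target effect of only 0.25 SD.

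**Working it through.** **The plan's own figure.** For d = 0.25, two-sided alpha 0.05 and 80% power, n per arm = 2(1.960 + 0.842)²/0.25² ≈ 251.2, so 252. Then 252/0.70 = 360 per arm, against the stated 362. Power at 253 per arm is 0.803. Also 724 × 0.70 = 506.8 and 362 × 0.70 = 253.4. The stated figures reproduce.

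**Assumptions, none given in the documents.** Standardised outcome, equal SDs at both visits, true effect zero, within-person correlation ρ of 0.3 to 0.7. Total dropout is 30% per arm and depends only on whether baseline is below or above the median (so MAR). Controls lose 20% of the low half and 40% of the high half. Intervention loses 30/30 (pattern A) or 40/20 (pattern B).

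**Baseline imbalance among completers, Δ.** The two halves of a standard normal have means ∓0.798.
- Control completers: (0.40 × (−0.798) + 0.30 × 0.798)/0.70 = −0.114.
- Intervention completers: 0 in A, +0.114 in B.
- Δ (intervention minus control) = 0.114 in A, 0.228 in B.

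**Bias by route.** A completer group with baseline mean m has expected follow-up mean ρm.
- Change score in completers: ρΔ − Δ = (ρ − 1)Δ.
- Independence model (all baselines, follow-up from completers only): ρΔ.
- Follow-up adjusted for baseline: ρΔ − ρΔ = 0. A joint model with unstructured covariance makes the same correction.

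| Pattern | Route | ρ = 0.3 | ρ = 0.5 | ρ = 0.7 |
|---|---|---|---|---|
| A | Change score | −0.080 | −0.057 | −0.034 |
| A | Independence | +0.034 | +0.057 | +0.080 |
| B | Change score | −0.160 | −0.114 | −0.068 |
| B | Independence | +0.068 | +0.114 | +0.160 |

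At ρ = 0.5 the SD of change is √(2(1 − 0.5)) = 1, so comparison with d = 0.25 is direct: 0.057/0.25 = 23% and 0.114/0.25 = 46%.

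**Effect on type I error (change score, ρ = 0.5).** The standard error with 253 per arm is √(2/253) = 0.0889. The shifts are 0.057/0.0889 = 0.64 and 0.114/0.0889 = 1.28 standard errors, so a nominal 5% test rejects about 10% and 25% of the time. Simulation with 362 randomised per arm gave 10% and 24%, and 5% with baseline adjustment.

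**Simulation with logistic dropout.** Here the true effect was −0.25 SD, dropout was 30% per arm, and the log-odds slope on baseline was 0 in control and 0.7 in intervention. The intervention arm now loses its high-baseline families, so the signs reverse. Ranges are over ρ = 0.3 to 0.7.
- Equal SDs: change score +0.06 to +0.14; independence −0.06 to −0.13. Unstructured likelihood, compound-symmetry likelihood, exchangeable GEE and baseline adjustment were all about 0.00.
- Follow-up SD 0.7 or 1.4 times baseline: exchangeable GEE off by about 0.02 to 0.05, compound symmetry by about 0.02 to 0.06, unstructured by about 0.00.
- Same slope (0.7) in both arms, equal SDs: every route about 0.00.

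**The case against.** The strongest reply is that section 12.3 also prescribes linear mixed models, and that it speaks of modelling outcomes over time. If the change-from-baseline sentence only means the group-by-time contrast in a model of both visits, the mixed-model route is sound under MAR given an adequate covariance. That is a fair reading, but it is not what the sentence says. The power calculation in section 14.4, a t-test of change in the remaining dyads, points the other way.

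The section also admits covariates associated with dropout. This helps only in part: it covers background demographics, not baseline need or baseline cortisol.

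Stronger readings that a reader might infer, and why they fail:
- *That every prescribed method loses validity under MAR.* Exchangeable GEE and compound symmetry were nearly unbiased at equal variances.
- *That the most restricted covariance means independence in the final model.* The protocol never names independence. The structure is a starting point followed by selection. In a model with a random intercept, the simplest residual structure still implies correlated visits. Akaike's criterion would be expected to favour correlation in likelihood models, although it cannot guide GEE or restore dropouts to a change score.
- *That section 19.2 undermines the whole analysis.* It concerns biological samples of people who refuse further participation. Survey outcomes are untouched, and much of the 30% may simply be loss of contact.
- *That the attrition check is deficient because it names patient characteristics and not arm* ("We will perform analyses to determine whether differential attrition occurred by patient characteristics"). This is detail that a statistical analysis plan can supply, as is the choice of working correlation.

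**Conclusion.** The point holds in limited form. The MAR statement in section 12.3 does not cover two analyses fixed beside it: the change score, which is complete-case with one follow-up visit, and unweighted GEE, which is not generally valid under MAR and is worst with an independence working correlation.

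The size is about 0.06 to 0.11 SD at ρ = 0.5, with the change-score and independence routes erring in opposite directions. It rests on assumed dropout that depends on baseline differently by arm; the protocol neither states nor excludes such a pattern. If the dependence is the same in both arms, the bias is about zero.

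Section 19.2 is a smaller inconsistency with the all-available-data statement, confined to biomarkers of those who refuse further participation. Severity is moderate: the remedy is simple, and it removes a dependence of the result on which sentence the analyst follows.

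**What to change.** In section 12.3:
- **Continuous outcomes:** replace the change-score dependent variable with a two-occasion linear mixed model of the baseline and 6-month values, with unstructured covariance and the group-by-time contrast as the treatment effect. Follow-up adjusted for baseline is an alternative that removes this bias equally.
- **Count or binary outcomes:** use a likelihood GLMM, or GEE after multiple imputation or inverse-probability weighting based on arm, language (the randomisation stratum) and the baseline outcome. State which outcome gets which model.
- **Covariance:** state that an independence structure may not be the final two-occasion model.

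Reconcile the sample-removal sentence in section 19.2 with the all-available-data statement in section 12.3 and with the consent form. Which rule applies is for the investigators to decide.

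The cost is a few sentences and slightly more programming. The sample size, visits and data collection do not change.
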